### Randomization and masking

Patients will be divided into two groups using simple randomization. This study will use a computerized random number generator in a 1:1 ratio to generate sequence numbers. Then, these sequence numbers will be coded and placed in sealed opaque envelopes. The researcher will divide the patients into an experimental or control group based on the sequence numbers in the envelope of their choice. The entire randomization process will be carried out by a researcher who is not involved in the intervention and data analysis. In addition, the study will also control for the possible effects of covariates by balancing baseline characteristics between the two intervention groups, which can reduce the biased results. Because this study adopts psychological interventions that make it difficult to implement blinding of participants and the researchers conducting the intervention, this study will be blinded only to the researchers assessing the outcomes.

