### Sample size and recruitment

In this study, the primary outcome of the psychological pain score was selected to calculate the effect sizes. Based on the literature [20], the post-intervention psychological pain score measured using DT was 1.5 ± 0.98 for the experimental group and 2.3 ± 1.05 for the control group, with a statistically significant difference, and an effect size d of 0.788 was calculated. In the G*Power software, the number of participants in each group sample was calculated as 35 cases by using two independent samples t-test and taking bilateral α = 0.05 and 1-β = 0.9. Considering a dropout rate of 20%, the minimum sample size was therefore derived as 84 patients, 42 in each group.

Nurses will introduce the study to depressed inpatients who meet the inclusion criteria, and if a patient agrees verbally to participate, nurses will notify the researchers. The researchers will explain the information about the study in more detail to participants, discuss the appropriate timing of the intervention, and provide informed consent. Then, the participant will return the signed informed consent to the researchers. Participants will be recruited from June 2022 to June 2023, and once recruited, patients will be randomly assigned to the experimental or control group.

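### Letting an envelope be chosen detaches allocation from the generated sequence, and simple randomisation has no mechanism for the baseline balancing that the plan describes

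*Protocol article*

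**What the plan says.** All of this is in the protocol article.

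- **Method** (Randomization and masking): "Patients will be divided into two groups using simple randomization". The list comes from a computer: "This study will use a computerized random number generator in a 1:1 ratio to generate sequence numbers".
- **Concealment** (same section): "these sequence numbers will be coded and placed in sealed opaque envelopes".
- **Assignment** (same section): "The researcher will divide the patients into an experimental or control group based on the sequence numbers in the envelope of their choice". The word *their* could refer to the patient or to the researcher.
- **Who does it** (same section): the process is "carried out by a researcher who is not involved in the intervention and data analysis". Recruitment is not among the exclusions.
- **Balance** (same section): the study will "control for the possible effects of covariates by balancing baseline characteristics between the two intervention groups". No stratification, blocking or minimisation is named.
- **Group size and timing** (Sample size and recruitment): "the minimum sample size was therefore derived as 84 patients, 42 in each group", and "once recruited, patients will be randomly assigned to the experimental or control group".
- **Adjustment** (Data analysis): the GEE is to be adjusted for baseline variables found to differ statistically between groups.
- **Schedule** (Data collection, Table 2): screening and consent are at -T1. Allocation and the baseline scales share the T0 column.

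**The concern.** A computer-generated list protects a trial because the nth eligible patient receives the nth assignment, and anyone can check this afterwards. If an envelope is chosen, that link is gone. A discarded envelope, a second draw or a preference for one envelope would leave no trace in the sequence.

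This matters more here than in a blinded trial. Patients and interveners know the arm, and Table 2 shows that all three primary outcomes (psychological pain, hope, cognitive distortion) are completed by the patient. Blinding the data collector therefore gives limited protection, and sound allocation carries most of the weight. No analysis can restore it later.

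The balancing sentence is a second difficulty. It stands among the allocation procedures, yet the stated procedure does nothing to bring it about. A reader cannot tell whether an unnamed restriction was used, or whether only adjustment in the analysis is meant.

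**Working it through.** **1. Envelope step.** Put the statements in order: list generated, numbers coded and sealed, envelope chosen, arm assigned. The third step makes the order of the list irrelevant. Under simple randomisation the assignments are independent, so a blind draw out of order still gives each patient a 1:1 chance. Randomness survives a blind draw; verifiability does not.

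**2. Independence of the randomiser.** Under Sample size and recruitment, nurses introduce the study, and researchers then explain it and obtain consent before assignment. The randomiser is a researcher kept apart from the intervention and the data analysis. Nothing says that this person is not also one of the recruiting researchers.

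**3. The plan's own sample size.** Inputs from Sample size and recruitment: 1.5 ± 0.98 versus 2.3 ± 1.05, two-sided α = 0.05, power 0.90, dropout 20%.

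- Pooled SD = √((0.98² + 1.05²)/2) = 1.0156; d = 0.8/1.0156 = 0.788, as stated.
- Noncentral t power: 0.893 at 34 per group and 0.901 at 35, so 35 is confirmed.
- 35 × 1.2 = 42 per group, 84 in total, as stated.

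**4. Split under simple randomisation.** Size of one arm X ~ Binomial(84, 0.5).

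- P(X = 42) = C(84, 42)/2⁸⁴ = 0.087.
- SD = √(84 × 0.25) = 4.58; 2.5% and 97.5% quantiles are 33 and 51.
- P(arms differ by 10 or more) = 2·P(X ≤ 37) = 0.326.

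**5. What an uneven split costs.** Noncentral t with noncentrality d·√(n₁n₂/(n₁+n₂)) and d = 0.788. For all 84 analysed, the noncentrality is 0.788 × √21 = 3.61 at 42:42 and 0.788 × √(1683/84) = 3.53 at 33:51.

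| Split | Power, all 84 analysed | Power after 20% loss in each arm |
|---|---|---|
| 42:42 | 0.946 | 0.889 |
| 37:47 | 0.943 | 0.885 |
| 33:51 | 0.936 | 0.875 |

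Averaged over all possible splits, power goes from 0.946 to 0.944 with 84 patients and from 0.901 to 0.897 with 70: about 0.2 and 0.4 percentage points.

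**6. Balancing.** Simple randomisation balances covariates in expectation but has no device that secures balance in the trial at hand. The only related step elsewhere is the adjustment under Data analysis. That acts after allocation and does not balance the groups.

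**The case against.** The strongest defence is that the safeguards are real. The numbers are coded, the envelopes are sealed and opaque, and the randomiser is kept apart from intervention and analysis. If *their* means the patient, a blind draw reveals nothing and remains random. A journal article may also leave envelope numbering and logging to the full protocol. Most of this stands. It does not remove the point, because choosing an envelope is a rule that the article states, not a detail that it omits.

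A reader might infer four stronger things that the document does not support:

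- *Allocation is not random.* A blind pick from sealed envelopes is random. The loss is verifiability, with room for selective picking.
- *The 42:42 split cannot be achieved.* The figure of 42 is a planning minimum, not an allocation rule. Simple randomisation meets it in expectation, and an uneven split costs little power. A fixed pool of 42 + 42 envelopes would give it with certainty, but that would no longer be simple randomisation.
- *Balancing means steering patients by their characteristics.* Nothing suggests this. The sentence speaks of controlling covariate effects and may loosely refer to the GEE adjustment.
- *Baseline scores were given with knowledge of the arm.* The shared T0 column leaves the order unstated, not wrong. Eligibility also needs OMMP and HAMD-24 scores, with screening at -T1, so psychological pain is scored once before allocation.

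**Conclusion.** The concern holds in a limited form. The envelope rule as written separates allocation from the generated order, so assignments cannot be verified and selective or repeated drawing cannot be ruled out. Independence from recruitment is not stated. The size of any resulting bias cannot be derived from the document, and there is no evidence that bias occurred.

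The balancing sentence has no mechanism behind it in the allocation procedure; the plan offers only adjustment at analysis.

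The effect on group sizes is real but small: an 8.7% chance of exactly 42:42, a 95% range of 33 to 51 for one arm, and about one percentage point of power lost at 33:51 with all 84 analysed (0.946 to 0.936). These figures assume independent 1:1 assignment of exactly 84 patients and the plan's d of 0.788. The case for changing the plan rests on the envelope step, not on the split.

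**What to change.** For patients not yet randomised:

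1. Use sequentially numbered, sealed, opaque envelopes, opened strictly in ascending order. Record patient ID and time before opening.
2. Open each envelope only after consent and all T0 scales are complete, and say so in the text and in Table 2.
3. Have this done by someone not involved in recruitment, where existing staff allow.

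In the text and analysis plan:

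4. Replace the balancing sentence with adjustment for prespecified baseline values, at least the baseline score of each outcome, in place of selection by baseline significance tests. The GEE now treats baseline as one of its repeated time points. If the baseline score becomes a covariate, it should leave the set of repeated responses.
5. Describe 42 per group as expected, not guaranteed. Permuted blocks are optional.
6. Report how the envelopes already used were drawn, by whom, and whether any were discarded or redrawn.

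Recruitment was planned from June 2022 to June 2023 and the article appeared in April 2023. On that schedule the new procedure reaches only the last patients, which makes item 6 essential. The cost is re-preparing the remaining envelopes and a short amendment, with no extra patients.

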### Intervention

#### The control intervention

Patients in the control group will be treated as usual (TAU) during hospitalization. TAU includes care for aspects of daily living, diet, safety, drug, and routine supportive psychology. Daily living care includes providing patients with a clean environment, instructing them on good personal hygiene, and exercising more. Since depressed patients are prone to binge eating or refusing to eat, patients will be instructed to eat at regular intervals and avoid stimulating foods. To ensure patient safety, nurses will strengthen the management of various hazardous materials and promptly assess the suicide risk of newly hospitalized patients and patients with changing conditions, and so on. Patients will be given health education about depression medicine and told to take their medication on time. Supportive psychological care refers to nurses listening patiently to what patients say, supporting and understanding them, encouraging them to live active life, etc.

#### The experimental intervention

Participants in the experimental group will receive TAU together with the PPSF intervention during hospitalization. The intervention is based on three dimensions of hope theory: goal cognition, pathway thinking, and agency thinking, and is supported by the use of SFBT questions during the intervention. We hope that combining positive intervention ingredients with well-used question techniques can increase positive cognition and ultimately reduce psychological pain. The PPSF intervener is a master of Nursing Specialist who has undertaken the SFBT subject training and is proficient in the practical application of the theory. Besides, the research nurse read the patient’s electronic medical records to understand the basic characteristics of the patient before intervention. The PPSF intervention will be conducted in six one-on-one, face-to-face sessions over two weeks, each lasting 30 to 40 min, along the six themes of instilling hope, agency thinking, path strategies, goal setting, cognitive reconstruction, and reinforcement of hope. Each session will focus on the theme of the positive ingredients, with the use of SFBT classical questions. Moreover, homework assignments such as breathing exercises, relaxation exercises, and positive thinking will be given at the end of each session. The detailed components of the PPSF intervention are shown in Table 1.

**Table 1 Tab1:** Outline of the PPSF intervention for patients with depression

Session 1	Implementer	Format (duration)	Theme	Instillation of hope: build trust and describe psychological pain
	Research nurse	Individual, face-to-face (30-40 min)	Content	1. Encourage patients to talk about their current psychological pain and explore the stressors of psychological pain 2. Instruct patients to perform simple deep breathing exercises
			SFBT questions	1. Normal question: What is your most serious psychological pain at the moment? Many patients in our unit suffer from psychological pain. Based on your description, psychological pain is affecting you greatly and it may be more helpful for you to discuss and learn how to let go of it during this intervention time together 2. Presuppositional question: What is the goal of this session? What can I do to help you in this situation?
			Homework	1. Make a list of psychological pain on a problem list and try to get the patient to normalize the pain and pay less attention to it 2. Perform simple deep breathing exercises on their own
Session 2	Implementer	Format (duration)	Theme	Agency thinking: uncover strengths and rebuild hope
	Research nurse	Individual, face-to-face (30-40 min)	Content	1. Watch a short video about hope and actively explore positive qualities such as hope and optimism 2. Instruct patients to perform imaginary relaxation training 3. Encourage patients to talk about touching or wonderful events they experienced during their growth stage, such as childhood memories, family happiness, career achievements, etc., emphasizing past strengths and resources
			SFBT questions	1. Strength exploration: if you think of yourself as the person you just described, what do you think are her strengths? 2. Exceptional question: what stage of growth was the happiest for you and what happened to make you feel happy? 3. Positive empowerment: what do you think your growing-up experience has given you?
			Homework	1. Recall what things reflect what strengths and characteristics of their growth, list three 2. Conduct independent imagination relaxation training
Session 3	Implementer	Format (duration)	Theme	Pathway strategy: social support and active response
	Research nurse	Individual, face-to-face (30-40 min)	Content	1. Ask the patients about the way they cope with psychological pain and how they have handled similar experiences in the past 2. Discuss how family members, friends, colleagues, and others have influenced and helped the patient during the illness or when experiencing certain things
			SFBT questions	1. Relationship question: Who do you have a better relationship with? Who will be the first person to discuss it if there is a problem? 2. Response question: every life struggles to adapt to its environment and grows upward no matter what the situation is, I believe you have taken some methods, can you talk about them specifically?
			Homework	1. Seek help from nurses, doctors, patients in the ward, parents, teachers, and classmates via cell phone and record it 2. Perform 3–5 min of brief positive breathing exercises on your own
Session 4	Implementer	Format (duration)	Theme	Determination of goals: set goals and focus on solutions
	Research nurse	Individual, face-to-face (30-40 min)	Content	1. Develop feasible short-term goals for specific psychological pain based on the patient’s strengths and in consultation with the patient 2. Discuss tips to achieve the goals and refine the sessions and steps to accomplish them
			SFBT questions	1. Focused Question: what problem is being solved today? 2. Change Question: if you start to change, what is the first thing we can see about you that has changed? 3. Miracle Question: imagine that a miracle happens when you are sleeping at night and the whole house is quiet. This miracle solves the problem you have been confused about while you were asleep. When you wake up the next day, what is the sign or change that lets you know that this miracle has indeed happened and that your problem has been solved?
			Homework	Review the content of this course, schedule the short-term goals set, form a behavior schedule, and record the completion of each day
Session 5	Implementer	Format (duration)	Theme	Reconstruction of cognition: evaluate progress and think positively
	Research nurse	Individual, face-to-face (30-40 min)	Content	1. Encourage patients to share their changes and progress and, thus, inspire confidence in change 2. Reflect on the meaning of the positive impact of the disease on life
			SFBT questions	1. Complimentary question: see the change in yourself? It is really special (recommended to use after you see a noticeable change) 2. Ruling question: now you are asked to rate yourself, how many points do you rate? 3. Guide the shift in thinking: how do you think this experience has helped you?
			Homework	1. Wake up every morning and say “believe in yourself” 3 times to yourself 2. Summarize the positive effects of the disease after this intervention
Session 6	Implementer	Format (duration)	Theme	Reinforcement of hope: look to the future and enhance hope
	Research nurse	Individual, face-to-face (30-40 min)	Content	1. Objectively summarize the gains and remaining problems throughout the intervention 2. Guide patients to express their expectations for the future
			SFBT questions	What are your feelings and thoughts about these interventions? Do you have plans after this consultation? This change means a lot to you and we see your power and ability to change. In what other areas do you think there might be changes?

### Outcome and outcome measures

#### Psychological pain

Psychological pain will be measured by the Chinese version of OMMP [45]. The scale has a total of 39 items with 8 factors. This scale is a Likert 5-point scale (from “never true in your case” to “true all of the time”), with higher scores associated with more severe psychological pain. Among depressed patients, the Chinese version of OMMP had the Cronbach’s alpha coefficient and the retest reliability of 0.974 and 0.814 [45], indicating high reliability.

#### Hope

Hope will be measured by the Chinese version of the Herth Hope Index (HHI) [46]. The scale contains three factors. The HHI has 12 items that are divided into three dimensions. Each item is rated on a Likert scale of 4 (from “strongly disagree” to “strongly agree”), with items 3 and 6 being reversed scores. The higher the score, the higher the level of hope. The Chinese scale has the Cronbach’s α coefficient of 0.874 and the re-test reliability of 0.925 in depressed patients [47].

#### Cognitive distortion

The Chinese version of the Cognitive Distortions Questionnaire(CDQ) [48] is applied to assess cognitive distortions in terms of both frequency and intensity. The scale is composed of 15 items, and each item is scored on a Likert 4-point (0–3) scale, with frequency ratings ranging from “no time” to “almost all the time” and intensity ratings from “don’t believe” to “believe a lot”. The total score was 0–75; the higher the score, the more obvious the distorted cognition. The Cronbach’s α coefficient and the re-test reliability of this Chinese scale are 0.85 in patients with depression [48].

#### Depression

The Chinese version of HAMD [49] is the most commonly used scale to assess depression and can better reflect the severity of depressive symptoms. Since there are several versions of HAMD, the 24-item version widely used in this hospital will be chosen. The Cronbach’s α coefficient and the re-test reliability of this Chinese scale are 0.646 and 0.979 in depressed patients [50].

#### Suicidal ideation

Suicidal ideation will be measured using the Self-Rating Ideation of Suicide Scale(SSIOSS) [51], which contains 26 items and 4 factors. The four factors are optimism, despair, masking, and sleep, and each entry is scored as “yes” or “no”. Suicidal ideation score was obtained by adding the scores of optimism factor, despair factor and sleep factor, and the higher the score, the stronger the suicidal ideation. The total score on the scale is 26, and a score of ≥ 12 indicated that the patient had suicidal ideation. The Chinese scale has the Cronbach’s α coefficient of 0.86 and the re-test reliability of 0.87 in undergraduates [51].

It should be explained that we did not include suicidal ideation in the outcomes when we registered at Chinese Clinical Trials.gov. However, later, we decided to add suicidal ideation as a secondary outcome, considering the strong relationship between psychological pain and suicide.

#### Other information

Other information included demographic information, clinical variables of patients, and reasons for dropout. Among them, demographic information includes participants’ gender, age, religion, education level, marital status, occupation, interpersonal relationship, and family history; Clinical variables include the type of diagnosis and medication prescribed for patients with depression. These two pieces of information are collected at the baseline. The reasons for attrition will be tracked and collected by researchers during the intervention.

### Data collection

The data collection for this study will be independently accomplished by a trained nurse who will be blind to recruitment and allocation. The study will measure outcomes at 5 time points: baseline, 1 and 2 weeks (post-intervention), and 1 month and 6 months after baseline (follow-up). The schedule of the study is shown in Table 2. As depressed inpatients are commonly hospitalized for 2–3 weeks, the first 3 measurements will be handed out on the spot in the ward, filled in, and collected. The last 2 measurements will be collected by appointment with patients in the outpatient clinic. All questionnaires will be issued in paper form and will be archived by special researchers after collection. If patients leave the wards earlier than 3 weeks, they will not be allowed to complete the questionnaire 3 times in the ward, and data collection will be completed by appointing patients to the outpatient clinic. Participants in the control group will also be required to complete the measurements at the same time points.

**Table 2 Tab2:** Schedule of enrolment, intervention, and outcome assessment

**Timepoint**	**Enrolment**	**Allocation**	**Post-allocation**				**Filler**
	-T_1_	T_0_ baseline	T_1_ 1st week	T_2_ 2nd week	T_3_ 1st month	T_4_ 6th month	
**Enrolment**:							
Eligibility screen	×						
Informed consent	×						
Allocation		×					
**Intervention:**							
Intervention			×	×			
control			×	×			
**Assessments:**							
Demographic information		×					
Psychological pain		×	×	×	×	×	patient
Hope		×	×	×	×	×	patient
Cognitive distortion		×	×	×	×	×	patient
Depression		×	×	×	×	×	researcher
Suicidal ideation		×	×	×	×	×	patient

